#### Additional parameters

Patients’ socio-demographic characteristics, including sex, employment status, living alone/with others, years since diagnosis, smoking status, alcohol consumption and healthy food intake will be collected by using questionnaires at baseline. Blood pressure, cholesterol levels, glycated haemoglobin (DM2 only) and medication use will be extracted from the patients’ charts at baseline. Characteristics of nurses, including age, level of nursing education, number of years of experience working as a primary care nurse, number of years working in the field of CVRM, achievement of self-management training and geographical area of the general practice will also be collected at baseline.

### Statistical analysis

#### Effectiveness of the activate intervention

Data will be analysed primarily according to intention to treat and secondarily according to per-protocol principles. All patients with outcome data will be included in the intention-to-treat analysis, regardless of their adherence to the intervention. Patients in the intervention group will be included in the per-protocol analysis if they received a minimum of three consultations (75%), based on the registration forms obtained from the nurses. Patients from both groups were excluded from this analysis if they did not complete the T1 measurement. To examine the effect of the Activate intervention between the arms, a multilevel analysis will be performed (three levels: time, participant and general practice). The continuous outcome data will be quantified by mean, SD and 95% CI using linear mixed effects models. For the binominal outcome data, risk ratios and 95% CIs will be estimated using generalised estimating equations (GEEs) with a log-link function. In case of non-convergence of a model, ORs will be estimated using a logistic mixed effects model. All mixed effects models include a random intercept for changes over time and between practices. An interaction term will be added for time and study arm. Missing data will be handled according to the rules of the questionnaires of missing data. Missing outcome data will not be imputed, because multilevel analysis is a flexible method for dealing with missing outcome data [59]. Sensitivity analyses, such as an analysis of protocol deviations, definitions of outcomes, and outliers, will be performed to assess the robustness of the findings.

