#### The Activate intervention

The Activate intervention is developed for patients at risk for CVD. The intervention is standardised in four nurse-led consultations to enhance physical activity—in the first week and after 2, 6 and 12 weeks—and will take place in the patient’s own general practice. Although the BCTs are systematically applied in the intervention, the content of the intervention will be individualised to the patient’s unique circumstances, needs and preferences by adapting the BCTs during the consultations (e.g., goal setting, action planning, feedback). The duration of the first consultation is 30 minutes, and the subsequent consultations last 20 minutes. During the first consultation, patients will receive a workbook containing information about the study, useful websites and apps, tips and tricks, activity logs and action plans.

In the first consultation, the nurses will discuss the patient’s CVD risk profile, the consequences of a sedentary versus an active lifestyle, and self-assessment of their activity level in order to raise awareness to improve the patient’s level of physical activity. Together, the patient and nurse formulate an overall outcome goal and an exercise goal, considering physical activity in minutes per day. In order to raise awareness of self-monitoring and how to self-monitor, the patient is asked to self-monitor physical activity during the next 2 weeks by using an accelerometer and a paper activity log, which provide feedback on the patient’s level of goal attainment. Additionally, the patient is asked to identify facilitators to goal attainment.

During the second consultation, the nurse rehearses the information about the consequences of an active lifestyle, reviews the goal attainment using the activity log kept by the patient, and discusses the identified facilitators. If applicable, the physical activity goal is re-formulated. A specific action plan to attain the level of physical activity formulated as their goal is set up. The patient is supported in finding ways to use facilitators for physical activity, is asked to self-monitor activities during the next weeks in order to attain the set physical activity goal, and is asked to identify possible barriers to goal attainment.

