### Care as usual

Patients in the control arm will receive care as usual, according to the national health care standards for patients at risk for CVD [16], during regular consultations with their nurse and will not receive additional consultations beyond standard of care to increase their physical activity level. Patients at risk for CVD have at least one consultation per year with their nurse; however, this frequency can be extended when considered necessary (e.g., in case of medication change). Patients with DM2 have at least four consultations with their nurse annually. In order to keep the nurses in the control arm motivated, the 1-day training will be offered to them at the end of the study.

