### Data collection

To assess the characteristics of the nurses participating in the study, a short questionnaire will be sent to nurses. To assess whether patients are eligible for improving their level of physical activity, patients are asked to fill out a short self-assessment using the SQUASH prior to consenting to participate in the study. Nurses will interpret the completed SQUASH using clear guidelines to see if a patient fits the inclusion criteria regarding insufficient level of physical activity. After enrolment, patient data will be collected at baseline (T0), after 3 months (T1) and after 6 months (T2) by use of an accelerometer, questionnaires and chart review (see Fig. 2). At time point T0, the nurses will distribute the questionnaires and accelerometer after enrolment during their regular scheduled visit. At time points T1 and T2, the research team will distribute the questionnaires and accelerometers. To maximize retention of general practices, the research team will contact each general practice regularly, and nurses can easily contact the research team for remarks and questions. Nurses will receive a monthly newsletter to keep them updated on the number of recruited patients in the other attending general practices and to invite them to share their experiences with other nurses. To maximize retention of patients, the research team will contact patients by telephone or e-mail if no questionnaire and accelerometer are received within 3 weeks. If the research team is not able to contact the patients after several attempts, we will ask the attending nurse to contact the patient. Furthermore, patients are encouraged to contact the research team if they have remarks and questions.

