### Outcome measures

#### Primary outcome

The primary outcome is physical activity objectively measured as the number of minutes of physical activity in the moderate to vigorous category. This will be assessed with a personal activity monitor (Pam AM300; Pam bv, Oosterbeek, The Netherlands) [46]. The Pam AM300 is a small, valid, and reliable triaxial accelerometer which can easily be worn on the hip. Additionally, patients will be asked to write down in a paper log the amount of minutes they have swum, cycled or done strength training, because the accelerometer cannot measure these activities accurately.

The number of minutes of physical activity in the moderate (3–6 metabolic equivalents [METs]) and vigorous (≥6 METs) categories at 6 month of follow-up will be considered as the primary outcome measure. Patients will be asked to wear the accelerometer during 7 consecutive days for 12 h daily at baseline (T0), at 3 months of follow-up (T1) and at 6 months of follow-up (T2). For a valid measurement, the accelerometer has to be worn for at least 4 weekdays and 1 weekend day for 8 h. After each data collection point, patients will be asked to send the accelerometer to the research team to upload the data from the accelerometer to a data file. The outcome is the average number of minutes of moderate to vigorous activity on all the valid days. With the Activate intervention, a mean difference in minutes of 20% of at least moderate level of physical activity from baseline is considered to be clinically relevant and reasonable to achieve within 3 months of intervention.

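### The secondary per-protocol analysis selects on attendance in one arm only and excludes patients without a 3-month measurement although the endpoint is at 6 months; the primary analysis is unaffected

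*Protocol article*

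**What the plan says.** Under Effectiveness of the activate intervention, the protocol article sets the order of the analyses: "Data will be analysed primarily according to intention to treat and secondarily according to per-protocol principles". The intention-to-treat analysis takes every patient with outcome data, whatever their adherence. The per-protocol set has two conditions.

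- Attendance, in the intervention arm only: "Patients in the intervention group will be included in the per-protocol analysis if they received a minimum of three consultations (75"%), counted from the nurses' registration forms.
- Measurement, in both arms: "Patients from both groups were excluded from this analysis if they did not complete the T1 measurement".

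Other sections bear on these rules.

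- Primary outcome: minutes in the moderate and vigorous "categories at 6 month of follow-up will be considered as the primary outcome measure". Data collection labels the 3-month visit T1 and the 6-month visit T2.
- The Activate intervention: the four consultations fall "in the first week and after 2, 6 and 12 weeks", so delivery ends at about T1.
- Care as usual: control patients "will not receive additional consultations beyond standard of care to increase their physical activity level".
- The model is a three-level linear mixed model over time, and "An interaction term will be added for time and study arm". Missing outcomes are not imputed; the article relies on the multilevel model to cope with them.

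**The concern.** Attending three of four activity consultations is behaviour that occurs after randomisation, and the outcome is also a voluntary health behaviour. Patients who keep coming may differ from those who stop in how their activity would have changed without any intervention. The rule removes the low attenders from one arm and leaves their counterparts among the controls in place. The article itself expects such variation: its Background says that many patients do not comply with interventions of this kind, and its process evaluation plans to describe who received the intervention and who dropped out.

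The T1 condition is a second selection after randomisation, and it does not match the endpoint. A patient who missed the 3-month measurement but has a valid 6-month value is removed although the primary outcome was observed.

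What is at stake is the reading of the secondary result. If it is larger than the intention-to-treat estimate, the reader cannot tell how much of the excess comes from receiving the consultations and how much from the selection.

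**Working it through.** **Scale, from Sample size calculation.** Mean 38 minutes, SD 18.1, target 20%: 0.20 × 38 = 7.6 minutes. Per arm, 2 × (1.96 + 0.8416)² × 18.1² / 7.6² = 2 × 7.849 × 327.61 / 57.76 = 89.04, which agrees with the stated 89. The design effect is 1 + (8 − 1) × 0.05 = 1.35. The point disputes none of these figures; they only set the scale.

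**One-sided attendance rule.** Suppose the intervention has no effect. Let q be the share of intervention patients below three consultations, and g the attender-minus-low-attender difference in the untreated outcome. The attenders' mean is A and the low attenders' mean is A − g. The controls contain both kinds, so their mean is (1 − q)A + q(A − g) = A − qg. The per-protocol contrast is A − (A − qg) = qg, although the true effect is zero.

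The article gives neither q nor g. Assuming q = 10–30% and g = 3.8–7.6 minutes (half to all of the target):

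| q | g (min) | shift qg (min) | share of 7.6 | two-sided type I error |
|---|---|---|---|---|
| 0.10 | 3.8 | 0.38 | 5% | 5.2% |
| 0.10 | 7.6 | 0.76 | 10% | 5.9% |
| 0.20 | 3.8 | 0.76 | 10% | 5.8% |
| 0.20 | 7.6 | 1.52 | 20% | 8.3% |
| 0.30 | 3.8 | 1.14 | 15% | 6.7% |
| 0.30 | 7.6 | 2.28 | 30% | 11.9% |

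The last column uses 279 × 0.85 = 237.15 patients in 31 practices, or 7.65 per practice. The design effect is 1 + 6.65 × 0.05 = 1.3325, so the effective number per arm is 237.15 / 1.3325 / 2 = 89.0. The standard error is 18.1 × √(1/89.0 + 1/(89.0(1 − q))). This treats the comparison as a single time point with SD 18.1, so the rates are rough.

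The meaning of g depends on the model. If the time-by-arm term is read as change from baseline, a stable difference in activity level between attenders and low attenders cancels. Then g is only the difference in untreated change, which may be smaller than the values tried here.

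**T1 rule against the T2 endpoint.** Taking patients who otherwise qualify:

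| T1 | T2 | in per-protocol set? | consequence |
|---|---|---|---|
| yes | yes | yes | none |
| yes | no | yes | still contributes to the mixed model through T1 |
| no | yes | no | an observed primary endpoint is discarded |
| no | no | no | no follow-up to lose |

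Only the third row is a loss. The model would accept these patients, and the article names that flexibility as its reason for not imputing. The number in this row cannot be derived from the article.

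**Threshold for a complier-average effect.** In Table 1, consultation 1 carries 8 of the 17 techniques, and 16 of 17 have appeared by consultation 2; only habit formation starts at consultation 3. Defining receipt as three or more consultations assumes that one or two have no effect. If 70% reach three and gain 7.6 minutes while the rest gain half of that, the intention-to-treat effect is 0.7 × 7.6 + 0.3 × 3.8 = 6.46. The complier estimate is then 6.46 / 0.7 = 9.2, about 1.6 too high. If the rest gain all of it, the estimate is 7.6 / 0.7 = 10.9, about 3.3 too high. The 70% and the gains are assumptions.

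**The case against.** An attendance rule in one arm is what any per-protocol set looks like when the comparator is usual care, and the analysis is declared secondary. This stands: the weakness is a known one of the method. It is a reason to label the result, and the article does not do so.

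A reader might infer that selected intervention patients are compared with wholly unselected controls. That is not so: controls without T1 are excluded too, and they are unselected only on attendance.

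A reader might also infer that T1 is simply the wrong visit. That is too strong. T1 marks the end of the consultations, Primary outcome calls the target reasonable to achieve within the 3-month intervention, and patients with T1 but no T2 still inform the model. What remains is an unexplained mismatch that discards some 6-month data.

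Finally, a reader might infer a bias towards benefit by construction. The direction depends on the untreated change in attenders and low attenders, which the article does not give. A contrast based on change from baseline would remove stable level differences.

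The planned sensitivity analyses on protocol deviations and the attendance records help with interpretation. They do not restore a randomised comparison or recover the patients excluded for a missing T1.

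**Conclusion.** The point holds for the secondary analysis. The per-protocol contrast is not protected by randomisation, because the attendance filter acts in one arm only. It probably favours the intervention if attenders would have had a better change in activity anyway. The size is unknown: 0.38–2.28 minutes, or 5–30% of the target, is an illustration resting on assumed exclusion shares and differences, and it may be smaller if the estimate is a change from baseline. Separately, the T1 condition removes patients with an observed 6-month outcome without a stated reason; how many is also unknown.

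It might be inferred that the trial's main conclusion is compromised. The article does not support that: the primary intention-to-treat analysis uses all patients with outcome data regardless of adherence, and neither filter touches it. Nor does the point justify replacing the per-protocol analysis with a complier-average effect at three or more consultations, because Table 1 makes an absence of effect below three implausible.

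**What to change.** 1. Delete the T1-completion exclusion. Any intervention patient meeting the consultation rule, and any control, with follow-up data enters the mixed model, and the T2 contrast is reported.
2. State that the per-protocol result is non-randomised and supportive.
3. Add, alongside the per-protocol analysis, a complier-average causal effect at T2 with allocation as instrument and practice-clustered standard errors. Define receipt as at least one consultation, and give the three-consultation threshold only as a sensitivity analysis. Non-compliance is essentially one-sided, because controls are not offered these consultations.

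The cost is a change of wording and one extra model with a wider confidence interval. No new data are needed: attendance is already on the nurses' registration forms. The article reports the trial as still collecting data, so the change can be made before analysis. If nearly all patients attend the first consultation, the complier-average estimate will lie close to the intention-to-treat estimate.

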## Methods/design

### Design

We designed a two-arm cluster randomised controlled trial with the general practice as the unit of randomisation to compare the Activate intervention with care as usual. Figure 1 shows a schematic overview of the trial design.

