#### Sample size calculation

The present trial is powered to detect a mean difference between the intervention arm and control arm of 20% in number of minutes of at least a moderate level of physical activity. Based on the results of the It’s LiFe! trial [61], the mean level of physical activity in participants is 38 minutes (SD 18.1). The It’s LiFe! trial is a three-arm trial performed in primary care in the Netherlands with patients with chronic obstructive pulmonary disease and DM2 in which the researchers aimed to increase physical activity with a self-management support programme and the It’s LiFe! tool (a monitoring and feedback tool). This study revealed an increase in physical activity of 27%, but only in the counselling and It’s LiFe! tool group, objectively measured with the Pam AM300. We consider an increase in physical activity of 20% as reasonable to achieve. Taking a power of 80% and a significance level of 5% into account requires 89 patients per arm. Assuming an intra-cluster correlation of 0.05 and a cluster size of 8 patients per general practice requires 30 or 31 participating practices [59]. Allowing a patient dropout rate of 15%, we aim to recruit 279 patients in total and 9 or 10 patients per general practice.

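### The primary mixed model names random intercepts only; if T0 is one of the outcomes, the arm-by-time test ignores any between-practice differences in change

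*Protocol article*

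**What the plan says.** Design describes a "two-arm cluster randomised controlled trial with the general practice as the unit of randomisation". Under Data collection, "patient data will be collected at baseline (T0), after 3 months (T1) and after 6 months (T2"). Minutes of moderate to vigorous activity "at 6 month of follow-up will be considered as the primary outcome measure".

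The section on effectiveness states that "a multilevel analysis will be performed (three levels: time, participant and general practice"). It then fixes the random part: "All mixed effects models include a random intercept for changes over time and between practices". The fixed part follows: "An interaction term will be added for time and study arm". For continuous outcomes it names no random slope, no practice-by-time effect, no robust variance and no baseline covariate.

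The sample size calculation does allow for clustering: "Assuming an intra-cluster correlation of 0.05 and a cluster size of 8 patients per general practice requires 30 or 31 participating practices".

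**The concern.** In a cluster trial, the standard error of the tested quantity must contain the variation of that quantity between practices. With T0 among the outcomes, the time-by-arm term at T2 is the difference between arms in mean change from T0. A random intercept takes the same value at every visit, so practice and patient intercepts both subtract out of a change. Despite the protocol's wording, an intercept cannot represent changes over time. What remains is residual variation within patients, pooled as if the changes of two patients in one practice were unrelated.

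The protocol gives its own reasons to expect practices to differ in change. The Background says that training does not always improve providers' skills enough and that poor uptake can weaken an intervention. The Discussion calls a competent provider essential to delivery, and the process evaluation measures fidelity. Nurses hand out the accelerometers at T0 and the research team does so at T1 and T2, so a practice's influence on measurement at T0 need not persist.

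At stake is the trial's main result: a p-value that is too small and a confidence interval that is too narrow.

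**Working it through.** **1. The plan's own figures.** The protocol states that "the mean level of physical activity in participants is 38 minutes (SD 18.1"), and the target is 20% of 38 = 7.6 minutes. With two-sided 5% and 80% power, 2 × (1.96 + 0.84)² × 18.1² / 7.6² ≈ 89 per arm, as stated. The design effect is 1 + (8 − 1) × 0.05 = 1.35, so 89 × 1.35 = 120.15 per arm, 240.3 in total, and 240.3 / 8 = 30.04 practices. The stated 30 or 31 is reproduced.

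**2. Variance of the change contrast.** Let c be the correlation of a practice's effect between visits. Let ρ be the correlation between visits of a patient's deviation from the practice level. Neither is in the protocol, so both are varied. A change T2 − T0 has

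- a practice part of 2σ² × ICC × (1 − c), and
- a patient part of 2σ² × (1 − ICC) × (1 − ρ).

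The ICC of change is therefore ICC(1 − c) / [ICC(1 − c) + (1 − ICC)(1 − ρ)]. With 8 patients per practice, the true variance divided by the modelled variance is about R = 1 + 7 × ICC of change. The type I error is about 2 × [1 − Φ(1.96 / √R)].

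**3. Numbers for ICC 0.05 and ρ = 0.6.**

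| c | ICC of change | R | Type I error |
|---|---|---|---|
| 1 | 0 | 1.00 | 5.0% |
| 0.8 | 0.010 / 0.390 = 0.026 | 1.18 | 7.1% |
| 0.5 | 0.025 / 0.405 = 0.062 | 1.43 | 10.1% |
| 0 | 0.050 / 0.430 = 0.116 | 1.81 | 14.6% |

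Simulation of 30 practices × 8 patients × 3 visits with no effect, analysed with random intercepts only, gave 4.9%, 7.2%, 10.2% and 14.5%.

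**4. Size of the standard error at c = 0.5.** The change variance per patient is 2 × 18.1² × 0.405 = 265.4. With 120 patients per arm, the modelled standard error is √(2 × 265.4 / 120) = 2.10 minutes. The true value is 2.10 × √1.43 = 2.52. Fitted mixed models gave 2.09 against 2.50.

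**5. Sensitivity.**

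- For ρ = 0.4 and 0.8, type I error is 6.4% and 9.2% at c = 0.8, and 8.5% and 14.6% at c = 0.5.
- For ICC 0.01, c = 0.5 and ρ = 0.6, the ICC of change is 0.005 / 0.401 = 0.0125, R = 1.09 and type I error is 6.0%. One simulation put it at about 5.5%. Over all c, and ρ from 0.4 to 0.8, ICC 0.01 gives 5% to 9%.
- If practice levels are stable but the intervention's effect varies between practices with SD 2, 3 or 4 minutes, rejection is 5.8%, 7.1% or 8.1%.
- With 31 practices of 9 patients, 15% of T2 values missing, c = 0.5 and ρ = 0.6, rejection was about 10.3%. Dropout does not remove the problem.

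**6. With practice variation in change allowed for.** A practice-level t-test of mean change with 30 − 2 = 28 degrees of freedom gave 4.1% to 5.5% in every scenario.

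**The case against.** The strongest reply is that the tested contrast is inferred. The protocol does not say that T0 is an outcome rather than a covariate, and it defines the primary outcome as minutes at 6 months. If the same random-intercept model is used to estimate the arm difference at T2 itself, the practice intercept does not cancel. Simulated type I error is then 4.9%, 5.2%, 5.5% and 6.7% at c = 1, 0.8, 0.5 and 0. This stands, and it makes the concern conditional. It does not remove it: a three-level model over time with a time-by-arm interaction and no baseline covariate reads most naturally as a comparison of change.

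A second reply is that the random-intercept sentence is loose wording in a condensed article, perhaps meaning participant and practice intercepts. That may be so. But the sentence states a rule for all mixed models rather than leaving one out. If a practice-by-time term was meant, the text does not say it.

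Some stronger inferences are not supported:

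- A reader might infer that the false-positive rate is certainly inflated. It is not if practice effects are stable.
- A reader might infer that losing the 1.35 design effect is itself the error. A change contrast has its own ICC, and R is 1.18 at c = 0.8 and 1.00 at c = 1.
- A reader might rely on each practice having a single nurse, or on practices measuring at different times. The protocol states neither.

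**Conclusion.** The point holds in conditional form. If T0 is among the outcomes, the stated random-intercept model gives a valid arm-by-time test only when practice effects do not change between visits. The protocol gives reasons to doubt that. At the planned ICC of 0.05 and ρ = 0.6, moderate instability (c from 0.8 to 0.5) puts the type I error at about 7% to 10%. The figure of 14-15% needs practices to keep no stable difference over six months and should be read as an outer bound for that ρ. With a small ICC, or if the arm difference at T2 is what is tested, the inflation is slight. The size rests on c and ρ, which the protocol does not give. The wording should be corrected because it governs the primary test, but this ranks below a defect that makes the planned analysis unusable: practice is already a level of the model and the remedy is simple.

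**What to change.** Replace the random-intercept sentence with one of two specifications, and name the arm contrast at T2 as the primary test.

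1. Model T1 and T2 as outcomes with T0 as a covariate, a practice random intercept, and a patient random intercept or unstructured within-patient covariance. The practice variance at follow-up then enters the standard error.
2. If T0 stays as an outcome, keep the participant and practice intercepts and add a practice-by-time random effect.

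Use Satterthwaite degrees of freedom in either case, since there are only about 30 practices.

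This needs no new data or patients. Trial status reports that data collection is still under way, so the change can be fixed before results are known. The cost is a somewhat wider confidence interval if practices do differ in change: with ρ = 0.6, relative to the interval from the stated model, by a factor of about √1.18 = 1.09 at c = 0.8 and √1.43 = 1.20 at c = 0.5 for the change contrast, before the small-sample correction.

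### As written, the primary mixed model most naturally estimates a difference in change from baseline; adjusting 6-month activity for baseline would be more precise at almost no cost

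*Protocol article*

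**What the plan says.** Under Effectiveness of the activate intervention, the Protocol article plans a linear mixed model with levels for time, participant and general practice, and random intercepts. It adds: "An interaction term will be added for time and study arm". It names no baseline covariate for this model. Data collection gives three occasions: T0 (baseline), T1 (3 months) and T2 (6 months). Baseline activity is named as a model term only under Potential effect modifiers, as one of seven characteristics examined in separate GEE models.

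The Primary outcome section fixes the time point: minutes in the moderate and vigorous "categories at 6 month of follow-up will be considered as the primary outcome measure". The same section describes the clinically relevant difference as 20% relative to baseline.

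The Sample size calculation is "powered to detect a mean difference between the intervention arm and control arm of 20% in number of minutes". It takes its inputs from an earlier trial, in which "the mean level of physical activity in participants is 38 minutes (SD 18.1").

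**The concern.** With arm, time and their interaction in the model, and arm means unconstrained at T0, the T2 interaction coefficient is the difference between arms in mean change from T0. That is a valid estimate of the effect, but it gives the baseline value a coefficient of exactly one. Whenever r is below 1, this over-corrects a chance baseline gap and spends precision that a regression on baseline would keep.

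The sample size rests on the SD of a level. The planned contrast has a different variance, and whether that is larger or smaller than the calculation assumed depends on r and on how practice effects behave over time. What is at stake is the width of the primary confidence interval and, under a low correlation, the planned 80% power.

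**Working it through.** **Reproducing the plan's figure.** The target is 0.20 × 38 = 7.6 minutes, with SD 18.1, two-sided 5% and 80% power. Sidedness is not stated; one-sided would give 71 per arm.

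- n per arm = 2 × [18.1 × (1.960 + 0.842) / 7.6]² = 89.04. The plan has 89.
- "Assuming an intra-cluster correlation of 0.05 and a cluster size of 8 patients per general practice requires 30 or 31 participating practices": design effect 1 + 7 × 0.05 = 1.35; 2 × 89 × 1.35 = 240.3; 240.3 / 8 = 30.04 practices.
- "Allowing a patient dropout rate of 15%, we aim to recruit 279 patients in total and 9 or 10 patients per general practice": 240 / 0.85 gives 283, against 279 = 31 × 9, which is close. Completers: 279 × 0.85 = 237.

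The sample size therefore reproduces as a comparison of levels at one time point. With 237 completers, power for that comparison is 79.5%.

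**Precision, same design effect for both analyses.** In units of the outcome variance, the factor is 2(1−r) for change and 1−r² for the baseline-adjusted comparison. The ratio is 2/(1+r). r is an assumption throughout, because the document gives none. Power is for 7.6 minutes with 237 completers and design effect 1.35.

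| r | 2(1−r) | 1−r² | Variance ratio | Power, change | Power, adjusted |
|---|---|---|---|---|---|
| 0.2 | 1.60 | 0.96 | 1.67 | 59.5% | 81.1% |
| 0.4 | 1.20 | 0.84 | 1.43 | 71.9% | 85.9% |
| 0.5 | 1.00 | 0.75 | 1.33 | 79.5% | 89.5% |
| 0.6 | 0.80 | 0.64 | 1.25 | 87.5% | 93.6% |
| 0.8 | 0.40 | 0.36 | 1.11 | 99.3% | 99.6% |

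**Precision, stable practice intercept.** A practice effect that is constant over time cancels from within-patient change, so change carries no design effect. Generalised least squares with three occasions, 30 practices of 8, ICC 0.05, and practice and participant intercepts gives the results below. The comparator, a model with baseline means held equal, stands in for baseline adjustment and also uses T1. The follow-up-only standard error is 2.715 (power 79.9%).

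| r | SE, change | SE, equal baseline | Variance ratio | Power, change | Power, equal baseline |
|---|---|---|---|---|---|
| 0.2 | 2.956 | 2.479 | 1.42 | 73.0% | 86.5% |
| 0.4 | 2.560 | 2.257 | 1.29 | 84.4% | 92.0% |
| 0.5 | 2.337 | 2.109 | 1.23 | 90.2% | 95.0% |
| 0.8 | 1.478 | 1.422 | 1.08 | 99.9% | 100.0% |

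**Break-even r, where change is as precise as the sample size assumed (factor 1.35).**

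- Stable practice intercept: 2(1−r) = 1.35, so r = 0.325.
- Full design effect on change: 2(1−r) × 1.35 = 1.35, so r = 0.50.
- Practice effect varying wholly by occasion: 2(1−r) + 2 × 7 × 0.05 = 1.35, so r = 0.675.

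**The case against.** The strongest reply is that the article does not say outright that T0 is in the outcome vector, that arm means are free there, or that the interaction at T2 is the primary estimate. The quoted sentence could sit in a model with T1 and T2 as outcomes and T0 as covariate, and an analysis plan that is not shown may say so. This stands as a limit on certainty. It does not remove the point, because the published model names no baseline term. If only T1 and T2 are outcomes and nothing is added, the interaction measures how the effect differs between 3 and 6 months. It is then not the 6-month effect, and baseline is still unused.

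A reader might infer that the trial is underpowered. The documents do not support that. They give no r, the sample size reproduces, and on the plainest reading of the practice random intercept the planned contrast has 84.4% power at r = 0.4 and 90.2% at r = 0.5. A reader might also infer that regression to the mean is large because activity is measured over one week. No reliability figure in the document supports this.

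It is also fair to say that both analyses are valid and that adjustment is not quite free. A valid accelerometer record needs at least 4 weekdays and 1 weekend day of 8 hours' wear, so some T0 values will be missing. A covariate model drops those patients unless a rule is set, whereas a repeated-measures model keeps them.

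**Conclusion.** The point holds as one of efficiency and clarity, with moderate confidence because the reading of the model is inferred. On the natural reading, the planned contrast is less precise than a baseline-adjusted one at every r below 1. The excess variance is 43% at r = 0.4, 33% at 0.5 and 11% at 0.8 under a common design effect, and 29%, 23% and 8% when a stable practice effect cancels. A fall below 80% power is a possibility only. It needs r below about 0.33, 0.5 or 0.68, according to whether the practice effect is stable, the full design effect applies to change, or the practice effect varies wholly by occasion. The planned analysis is not invalid and the sample size needs no correction, but the plan gives up precision that data already being collected would supply.

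**What to change.** State the primary analysis as moderate-to-vigorous minutes at T1 and T2 in the three-level mixed model, with T0 minutes as a fixed covariate, arm, time and arm by time, and name the arm difference at T2 as the primary estimate. Do the same for each continuous secondary outcome with its own baseline.

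Prefer the covariate to a model that constrains arm means to be equal at T0. Practices are allocated on joining, intervention nurses are trained before patients are included, and unblinded nurses then check eligibility and enrol. Equal expected baselines are therefore not assured. The covariate conditions on the observed value without asserting equality, although neither approach removes selection at enrolment.

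Add a rule for patients without valid T0 wear, for example mean imputation of the covariate, so that they stay in the analysis. The cost is a change of wording and that one rule; no new data are needed.
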